**Safety reporting**

As this study is testing the impact of an educational intervention on selected non-invasive outcome measures, no adverse events or complications associated with this intervention are expected. We consider that the administration of the questionnaire, the health hygiene education intervention, and the collection of the stool specimen will have no safety effect.

With respect to the routine deworming program, it may be that the deworming pill has a minor transitory side effect. The proposed anthelmintic, albendazole, has an excellent safety record involving over billions of doses [7, 42]. This drug is considered very safe and its administration is not a concern. Mass deworming of school children with albendazole is recommended by WHO, UNICEF, and the World Bank, among other organizations. Because of its overwhelmingly benefits, in 2001, The World Health Assembly unanimously ratified the resolution that deworming should reach at least 75% of all school children in endemic areas by the year 2010. Nevertheless, we will ensure that the local health authorities are informed about our deworming activities. We have collaborated with them in the past and will continue to do so throughout this research.

**Anticipated benefits**

It is anticipated that all schools and students participating in the research will benefit from this study. Schools will benefit directly because the capacity-building workshops and the education intervention program will provide them with new knowledge and tools to address STH infections, and indeed, other health hygiene concerns. Students participating in the study will also benefit directly from the study because they will be given the opportunity of increased knowledge. School absenteeism is expected to be reduced, benefiting students, schools, families and their community. As our previous study demonstrated, 86% of grade 5 students in Belén are infected by at least one parasites species [2]. Participation in this study will therefore contribute to improved health status.

**Potential risks**

As the planned intervention will consist of a health hygiene education program, there are no associated risks. There are also no associated risks with the data collection procedures (questionnaires and provision of stool specimens).

**Privacy and confidentiality**

Participants and schools will be assigned an identification number for the duration of the study to ensure the confidentiality of any results. All original documents, including questionnaires and informed consent forms, will be kept (in Peru) in a locked cabinet and room. All electronic information, such as databases, will be stored on a password-protected computer in a locked room. Access to original documents and electronic information will initially be restricted to the Project Director, Principal Investigator and study coordinators only.

**Ethical oversight**

The principal investigator, Project Director, study coordinators and all other research personnel will conduct the study in an ethical manner which is consistent with the international principles of good practice and will function according to institutional policies of the McGill University Health Centre and the Asociación Civil Selva Amazónica, governing human subjects’ research, applicable research guidelines and in compliance with the law. The research investigators understand that the study is subject to review and approval from both the Research Ethics Board in Canada and the Dirección de Salud de Loreto in Peru.

The trial will be registered according to international regulations.

**Compensation**

No financial or other incentives or compensation will be given to any study participant. At the end of the trial, participating schools will keep all educational materials used. The principal investigator and project director will also facilitate access to additional educational materials, as requested by the schools.

**Results dissemination**

The results of this trial will be published and presented in national and international fora, including scientific conferences and peer-reviewed journals. Dissemination in local, regional and national media in Peru will also be explored. The results will be of interest to all 129 other STH-endemic countries who are currently, or who are planning to, implement a school-based deworming program. Therefore, our results will be sent to newsletters such as Action Against Worms, the Deworm the World initiative, the Partners for Parasite Control, etc.

**Funding**

This study is supported by an Interdisciplinary Capacity Enhancement grant from the Canadian Institutes of Health Research ([name]). Funding continues to 2011.

**Chronogram of research activities**

The following table provides the detailed schedule of all research activities, with approximate start and end dates.

|  | **2009** | | **2010** | | | | | | | | | | | |
| --- | --- | --- | --- | --- | --- | --- | --- | --- | --- | --- | --- | --- | --- | --- |
| **Activities** | November | December | January | February | March | April | May | June | July | August | September | October | November | December |
| Preliminary school visits | ✓ | ✓ |  |  |  |  |  |  |  |  |  |  |  |  |
| Ethics approval (Canada and Peru) |  | ✓ | ✓ | ✓ |  |  |  |  |  |  |  |  |  |  |
| Trial registration |  |  |  | ✓ |  |  |  |  |  |  |  |  |  |  |
| Informing health authorities; meeting all school principals |  |  |  | ✓ |  |  |  |  |  |  |  |  |  |  |
| Randomization |  |  |  | ✓ |  |  |  |  |  |  |  |  |  |  |
| Training workshops for teachers in the intervention schools |  |  |  | ✓ | ✓ |  |  |  |  |  |  |  |  |  |
| Organization of meetings with parents (informed consent) |  |  |  |  | ✓ |  |  |  |  |  |  |  |  |  |
| Baseline survey (questionnaire, weight and height, stool specimen) – before deworming |  |  |  |  |  | ✓ |  |  |  |  |  |  |  |  |
| Deworming |  |  |  |  |  | ✓ |  |  |  |  |  |  |  |  |
| Start of the education program in the intervention schools |  |  |  |  |  | ✓ | ✓ | ✓ | ✓ | ✓ |  |  |  |  |
| Cure rate estimation (2 weeks post-deworming) |  |  |  |  |  |  | ✓ |  |  |  |  |  |  |  |
| Second survey (questionnaire, weight and height, stool specimen) |  |  |  |  |  |  |  |  |  | ✓ |  |  |  |  |
| Training workshop of the education program offered to control schools |  |  |  |  |  |  |  |  |  | ✓ |  |  |  |  |
| Health education program offered to control schools |  |  |  |  |  |  |  |  |  | ✓ | ✓ | ✓ | ✓ |  |
| Data analysis |  |  |  |  |  |  |  |  |  |  | ✓ | ✓ | ✓ |  |
| Begin dissemination of results |  |  |  |  |  |  |  |  |  |  |  |  |  | ✓ |

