**Sample size justification**

Based on our survey of schools in Belén, 18 schools are eligible and have already demonstrated an interest in participating in the study. They have a total of 1438 students enrolled in Grade 5 (Table 2). Power calculations are based on the formula for logistic regression with a single binary covariate (i.e. the education intervention) and the Wald test was used as the basis for computations [39]. Based on our past parasitological Belén school surveys a response rate of 80.6% is expected [2]. A 5% loss to follow-up is also assumed during the 4-month period. Thus, we estimate a sample size of 1101 participating students, distributed in the 18 schools.

In addition, the power calculations must take into account within-school clustering. The intraclass correlation coefficient (ICC) represents the proportion of the total variance that is accounted for by between-cluster rather than within-cluster variation and can be used to calculate the Effective Sample Size (ESS). Because we could not find any reported ICC of within-school clustering of STH re-infection in the literature, we re-analysed the original database of [name] et al. [2], which contained the parasitological results of 1074 Belén students, and calculated the within-school ICC of STH prevalence (as an estimation of ICC of re-infection rates). The ICC was calculated using STH prevalence as the outcome and the school as the grouping factor, while adjusting for age, sex, and the school ecological zone (floodplain or upland). The obtained ICC had a value of 0.028 which resulted in an ESS of 412 and an associated design effect of 2.7. Power was estimated assuming that 50% of children will be exposed to the intervention and that the re-infection rate in the control group will be 49.5%. The latter is based on the reported 3-month re-infection rate of Malaysian school-children treated with albendazole [40]. Thus, the proposed study has good power (80.3%) to detect a moderate effect (i.e., OR=1.75) and has an excellent power (93.4%) to detect a strong effect, corresponding to an OR of 2.00.

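### Schools are randomised before parents are asked for consent, with no stated concealment, so participation could differ by arm and bias the comparison

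*Protocol*

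**What the plan says.** The Chronogram of research activities gives this order for 2010, with dates it calls approximate:

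- February: randomisation of schools.
- February and March: "Training workshops for teachers in the intervention schools".
- March: "Organization of meetings with parents (informed consent".
- April: "Baseline survey (questionnaire, weight and height, stool specimen) – before deworming", then deworming and the start of the education programme.

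Under Study design, the school is the unit of allocation, stratified by size. Under Study population, entry is individual: written parental consent and verbal assent are required for each child. Assent has no row of its own in the chronogram. The questionnaire (Annex 6) confirms both consent and assent before its first question, which at baseline means April.

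The Measurements section blinds the technologists who read the stool slides. It makes no such statement for those who seek consent or conduct the interviews. Planned statistical analyses describes an intention-to-treat analysis of all children in both arms, adjusted for named covariates and for any baseline imbalance.

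On participation, the Sample size justification states: "Based on our past parasitological Belén school surveys a response rate of 80.6% is expected". It counts later attrition separately: "A 5% loss to follow-up is also assumed during the 4-month period".

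**The concern.** In a cluster trial, randomising schools protects the comparison only if the children who enter are not selected differently in the two arms. Here every individual decision to enter comes after the school has been allocated. By the time parents are approached, training of intervention-school teachers has at least begun. If this makes teachers, staff or parents in one arm more or less inclined to secure consent, the two groups of participants may differ in underlying risk of re-infection.

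The planned analysis cannot fully repair this. An intention-to-treat set can contain only children who consented, so it starts after the selection has happened. Covariate adjustment deals only with measured differences among participants. At stake is the validity of the primary comparison; the sample size figures are not affected.

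**Working it through.** **Inputs from the protocol** (Sample size justification and Table 2): 1438 enrolled children; 80.6% expected response; 5% loss to follow-up; control re-infection 49.5%; target OR 1.75; effective sample size 412, with half exposed (206 per arm).

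**1. The plan's participant count.** 1438 × 0.806 = 1159, and 1159 × 0.95 = 1101. This agrees with the stated result: "Thus, we estimate a sample size of 1101 participating students, distributed in the 18 schools".

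**2. Children who may not enter.** 1 − 0.806 = 19.4%, or 1438 − 1159 = about 279 children. This is separate from the 5% lost later.

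**3. Planned difference.** Control odds are 0.495/0.505 = 0.980. Dividing by 1.75 gives 0.560, so the intervention rate is 0.560/1.560 = 35.9%. The difference is 49.5 − 35.9 = 13.6 points.

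**4. Size of a possible bias.** The documents give no difference in participation by arm and no risk for non-participants, so both inputs are assumptions. Let one arm participate at 80.6%. Let the other recruit a further share x of enrolled children, whose re-infection risk exceeds that of the other participants by d. That arm's rate then shifts by

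bias = x × d / (0.806 + x)

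| x | d | Bias |
| --- | --- | --- |
| 0 | any | 0 |
| 0.05 | 0.10 | 0.005/0.856 = 0.6 points |
| 0.10 | 0.20 | 0.020/0.906 = 2.2 points |

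**5. Scale.** The range is 0.6/13.6 = 4% to 2.2/13.6 = 16% of the planned difference. The standard error of the difference under no effect is √(2 × 0.495 × 0.505/206) = 4.9 points, so the upper value is 2.2/4.9 = 0.45 standard errors. At that shift the two-sided 5% test rejects a true null with probability Φ(−1.96 + 0.45) + Φ(−1.96 − 0.45) = 0.066 + 0.008, or about 7%.

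The sign depends on which arm recruits more and on whether the extra children are at higher or lower risk. Neither is known.

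**The case against.** The strongest reply is that this design leaves little room for recruitment bias. The target is the whole Grade 5 enrolment of 18 named schools that had already shown interest, so nobody finds or picks children after allocation. Education is delivered by class, deworming is routine in both arms, the measurements are the same, and control schools are offered the programme later. A parent has little reason to consent differently by arm. This stands, and it narrows the risk to differential consent, assent or specimen return. It does not remove the risk, because nothing stated keeps participation equal.

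Three stronger readings are tempting, but the documents do not support them.

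- **That baseline knowledge and behaviour are already altered by the intervention.** Study design starts the education after deworming, and the chronogram places the baseline survey before deworming. Only teachers attend workshops earlier. Informal spill-over to pupils is conceivable, but no section describes it.
- **That parents and consent staff know the arm.** No section says so, and the consent forms are not in the copy reviewed. Workshops and consent meetings also overlap in March, so training need not be complete when parents are asked. What is established is that randomisation comes first and no concealment is stated.
- **That the full 19.4% are refusals made in knowledge of the arm.** The 80.6% comes from past parasitological surveys and is not split into refusals and missing specimens. It says nothing about a difference between arms. Specimen collection, however, also follows allocation.

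A much larger distortion can be constructed. With no true effect, a spurious OR of 1.47 arises if non-participants differ from the 49.5% rate by 20 points in opposite directions in the two arms. Nothing in the protocol points to such a pattern.

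**Conclusion.** The point holds as a risk to validity. The protocol schedules individual entry after school allocation and states no concealment at recruitment, and its analysis cannot restore comparability lost at that stage. Up to 19.4% of enrolled children may not enter.

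The illustrative bias of 0.6 to 2.2 points is modest against 13.6 and rests wholly on the assumed inputs. Its direction is unknown, and it is zero if participation does not differ by arm. This does not invalidate the trial, but it should be corrected because the remedy is cheap and has to be in place before recruitment.

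**What to change.** Reorder the chronogram as follows:

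1. Close the signed consent and assent lists in all 18 schools in March.
2. Randomise. Stratification needs only school size, which Table 2 already gives.
3. Hold the intervention-teacher workshops after randomisation and before education starts, which is after deworming in April.

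Deworming and follow-up dates stay as they are. Assent would have to be taken with consent in March, not left to the baseline interview.

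If the order cannot change, state that consent staff and parents are kept unaware of allocation until the lists close, and compare participation by arm against enrolment.

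The cost is a shorter workshop window: training now spans February and March, and would have to fit into the weeks between closing the lists and the start of education, close to the April baseline fieldwork.

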**Annex 5**

Questionnaire (Spanish Version)

**Annex 6**

Questionnaire (English Version)

**Annex 5:** Questionnaire (Spanish Version)

**Efectividad de una intervención educativa, post desparasitación, para reducir las lombrices y la inasistencia en los escolares de 5^to^ grado, Belén**

**Identificación de la escuela, niño(a), entrevistador**

| Institución educativa  _____________________  Nombre del profesor /clase  ______________________ | Nombre del niño/a  _________________________________  Código de identificación   \|  \| \| --- \| | entrevistador  _____________________  fecha de entrevista (dd/mm/aaaa)   \| **/ /** \| \| --- \| |
| --- | --- | --- | --- | --- |

**criterios de elegibilidad**

| **A** | ¿Tiene consentimiento de sus padres? | \| **⃞** \| Si \| *Realice la pregunta B* \| **⃞** \| No \| *Excluir su participación* \| \| --- \| --- \| --- \| --- \| --- \| --- \| |
| --- | --- | --- | --- | --- | --- | --- | --- | --- |
| **B** | ¿Tiene asentimiento del niño? | \| **⃞** \| Si \| *Realice la pregunta 1* \| **⃞** \| No \| *Excluir su participación* \| \| --- \| --- \| --- \| --- \| --- \| --- \| |

**Medidas tomada por el entrevistador**

| **1** | ¿Indique en qué turno está matriculado el niño? | \| **⃞** \| Mañana \| (1) \| **⃞** \| Tarde \| (2) \| **⃞** \| Noche \| (3) \| \| --- \| --- \| --- \| --- \| --- \| --- \| --- \| --- \| --- \| |
| --- | --- | --- | --- | --- | --- | --- | --- | --- | --- | --- | --- |
| **2** | ¿Cuál es el sexo del niño? | \| **⃞** \| Femenino \| (1) \|  \| **⃞** \| Masculino \| (0) \| \| --- \| --- \| --- \| --- \| --- \| --- \| --- \| |
| **3** | ¿Cuándo es tu cumpleaños? (dd/mm/aaaa) | \| **/ /** \| Edad \|  \| *No sabe* \| **⃞** \| \| --- \| --- \| --- \| --- \| --- \| |
| **4** | Peso del niño | \|  \|  \| Kg \|  \| *No se peso* \| **⃞** \| \| --- \| --- \| --- \| --- \| --- \| --- \| |
| **5** | Talla del niño | \|  \|  \| Talla \|  \| *No se tallo* \| **⃞** \| \| --- \| --- \| --- \| --- \| --- \| --- \| |
| **6** | ¿Tiene las uñas sucias o largas? | \| **⃞** \| Si \| (1) \| **⃞** \| No \| (0) \| **⃞** \| *No sabe* \| (99) \| \| --- \| --- \| --- \| --- \| --- \| --- \| --- \| --- \| --- \| |

**Nivel de conocimiento sobre los bichos**

| **i** | **A-** ¿Conoces cómo se transmiten los bichos (parásitos intestinales)? | | | | \| **⃞** \| Si \| (1) \|  \| **⃞** \| No \| (0) \| \| --- \| --- \| --- \| --- \| --- \| --- \| --- \| | |
| --- | --- | --- | --- | --- | --- | --- | --- | --- | --- | --- | --- | --- | --- |
|  | **B-** ¿Si, cómo?   \| **⃞** *No aplica (NA)* \| \| --- \| | \| 1) \|  \| \| --- \| --- \| \| 2) \|  \| \| 3) \|  \| \| 4) \|  \| | | | | |
| **II** | **A**- ¿Conoces por qué los bichos son dañinos para tu salud? | | | | \| **⃞** \| Si \| (1) \|  \| **⃞** \| No \| (0) \| \| --- \| --- \| --- \| --- \| --- \| --- \| --- \| | |
|  | **B-** ¿Si, Por qué son dañinos?   \| **⃞** *No aplica (NA)* \| \| --- \| | | | \| 1) \|  \| \| --- \| --- \| \| 2) \|  \| \| 3) \|  \| \| 4) \|  \| | | |
| **III** | **A**- ¿Conoces cómo puedes evitar los bichos? | | | | | \| **⃞** \| Si \| (1) \|  \| **⃞** \| No \| (0) \| \| --- \| --- \| --- \| --- \| --- \| --- \| --- \| |
|  | **B-** ¿Si, cómo?   \| **⃞** *No aplica (NA)* \| \| --- \| | | \| 1) \|  \| \| --- \| --- \| \| 2) \|  \| \| 3) \|  \| \| 4) \|  \| | | | |

**Encuesta sobre factores de riesgo**

| **7** | | **A-** ¿En qué comunidad /localidad vives?  **B-** ¿En qué calle, pasaje, manzana, sector o lote se ubica tu casa? | | \| Localidad: .................................................. \| **⃞** *No sabe* (99) \| \| --- \| --- \| \| Ubicación: .................................................  .................................................................... \| **⃞** *No sabe* (99)  **⃞** *No aplica* (NA) \| | |
| --- | --- | --- | --- | --- | --- | --- | --- | --- | --- |
| **8** | | ¿Tu casa está hecha de material noble o rústica? | | \| **⃞** \| Noble \| (1) \| **⃞** \| Rústica \| (0) \| **⃞** \| *No sabe* \| (99) \| \| --- \| --- \| --- \| --- \| --- \| --- \| --- \| --- \| --- \| | |
| **9** | | ¿En tu casa, cocinan con gas, kerosene, carbón, o leña? | | \| **⃞** \| Gas \| (0) \| **⃞** \| Carbón \| (2) \| **⃞** \| Otros_____ \| (4) \| \| --- \| --- \| --- \| --- \| --- \| --- \| --- \| --- \| --- \| \| **⃞** \| Kerosene \| (1) \| **⃞** \| Leña \| (3) \| **⃞** \| *No sabe* \| *(99)* \| | |
| **10** | | ¿Tienes energía eléctrica en casa? | | \| **⃞** \| Si \| (1) \| **⃞** \| No \| (0) \| **⃞** \| *No sabe* \| (99) \| \| --- \| --- \| --- \| --- \| --- \| --- \| --- \| --- \| --- \| | |
| **11** | | ¿Tienes radio en casa? | | \| **⃞** \| Si \| (1) \| **⃞** \| No \| (0) \| **⃞** \| *No sabe* \| (99) \| \| --- \| --- \| --- \| --- \| --- \| --- \| --- \| --- \| --- \| | |
| **12** | | ¿Tienes televisor en casa? | | \| **⃞** \| Si \| (1) \| **⃞** \| No \| (0) \| **⃞** \| *No sabe* \| (99) \| \| --- \| --- \| --- \| --- \| --- \| --- \| --- \| --- \| --- \| | |
| **13** | | **A-** ¿Tienes agua potable en tu casa (agua de grifo)? | | \| **⃞** \| Si \| (1) \| **⃞** \| No \| (0) \| **⃞** \| *No sabe* \| (99) \| \| --- \| --- \| --- \| --- \| --- \| --- \| --- \| --- \| --- \| | |
|  |  | **B-** ¿En caso que no, de dónde se abastecen de agua en tu casa?   \| **⃞** *No aplica (NA)* \| \| --- \| | | \| **⃞** \| Grifo vecino \| (0) \|  \| **⃞** \| Tanque \| (4) \| \| --- \| --- \| --- \| --- \| --- \| --- \| --- \| \| **⃞** \| Río \| (1) \|  \| **⃞** \| Pileta publica \| (5) \| \| **⃞** \| Pozo \| (2) \|  \| **⃞** \| Otros____________ \| (6) \| \| **⃞** \| Cisterna \| (3) \|  \| **⃞** \| *No sabe* \| (99) \| | |
| **14** | | ¿En casa tomas agua directo o tratada (hervida o clorada)? | | \| **⃞** \| Directo \| (1) \| **⃞** \| Tratada \| (0) \| **⃞** \| *No sabe* \| (99) \| \| --- \| --- \| --- \| --- \| --- \| --- \| --- \| --- \| --- \| | |
| **15** | | ¿Tu baño se ubica adentro o afuera de tu casa? | | \| **⃞** \| Adentro \| (1) \| **⃞** \| Afuera \| (0) \| **⃞** \| *No sabe* \| (99) \| \| --- \| --- \| --- \| --- \| --- \| --- \| --- \| --- \| --- \| | |
| **16** | | ¿Tu baño está conectado a tubo de desagüe, a caño, a río, o a pozo ciego? | | \| **⃞** \| Desagüe \| (0) \| **⃞** \| Río \| (2) \| \| --- \| --- \| --- \| --- \| --- \| --- \| \| **⃞** \| Caño \| (1) \| **⃞** \| Pozo ciego o silo \| (3) \| \| **⃞** *No sabe* (99) \| \| \| \| \| \| | |
| **17** | | ¿Te bañas en el río Itaya – siempre, a veces, o nunca? | | \| **⃞** \| Siempre \| (0) \| **⃞** \| Nunca \| (2) \| \| --- \| --- \| --- \| --- \| --- \| --- \| \| **⃞** \| A veces \| (1) \| **⃞** \| *No sabe* \| (99) \| | |
| **18** | | ¿Haces el dos en campo abierto (huerta o patio) - siempre, a veces, o nunca? | | \| **⃞** \| Siempre \| (0) \| **⃞** \| Nunca \| (2) \| \| --- \| --- \| --- \| --- \| --- \| --- \| \| **⃞** \| A veces \| (1) \| **⃞** \| *No sabe* \| (99) \| | |
| **19** | | ¿Te limpias con papel higiénico cuando haces el dos - siempre, a veces, o nunca? | | \| **⃞** \| Siempre \| (0) \| **⃞** \| Nunca \| (2) \| \| --- \| --- \| --- \| --- \| --- \| --- \| \| **⃞** \| A veces \| (1) \| **⃞** \| *No sabe* \| (99) \| | |
| **20** | | **A-** ¿Te lavas las manos después de ir al baño – siempre, a veces, o nunca?  **B-** ¿Cómo te lavas las manos después de ir al baño -con agua sola o jabón y agua?   \| **⃞** *No aplica (NA)* \| \| --- \|   **C-** ¿Si es con jabón, lo usas siempre, a veces, o nunca?   \| **⃞** *No aplica (NA)* \| \| --- \| | | \| **⃞** \| Siempre \| (0) \| **⃞** \| Nunca \| (2) \| \| --- \| --- \| --- \| --- \| --- \| --- \| \| **⃞** \| A veces \| (1) \| **⃞** \| *No sabe* \| (99) \|  \| **⃞** \| Agua \| (0) \| **⃞** \| Jabón y agua \| (1) \| **⃞** \| *No sabe* \| (99) \| \| --- \| --- \| --- \| --- \| --- \| --- \| --- \| --- \| --- \|  \| **⃞** \| Siempre \| (0) \| **⃞** \| Nunca \| (2) \| \| --- \| --- \| --- \| --- \| --- \| --- \| \| **⃞** \| A veces \| (1) \| **⃞** \| *No sabe* \| (99) \| | |
| **21** | | **A-** ¿Te lavas las manos antes de comer – siempre, a veces, o nunca?  **B-** Cómo te lavas las manos antes de comer -con agua sola o jabón y agua?   \| **⃞** *No aplica (NA)* \| \| --- \|   **C-** ¿Si es con jabón, lo usas siempre, a veces, o nunca?   \| **⃞** *No aplica (NA)* \| \| --- \| | | \| **⃞** \| Siempre \| (0) \| **⃞** \| Nunca \| (2) \| \| --- \| --- \| --- \| --- \| --- \| --- \| \| **⃞** \| A veces \| (1) \| **⃞** \| *No sabe* \| (99) \|  \| **⃞** \| Agua \| (0) \| **⃞** \| Jabón y agua \| (1) \| **⃞** \| *No sabe* \| (99) \| \| --- \| --- \| --- \| --- \| --- \| --- \| --- \| --- \| --- \|  \| **⃞** \| Siempre \| (0) \| **⃞** \| Nunca \| (2) \| \| --- \| --- \| --- \| --- \| --- \| --- \| \| **⃞** \| A veces \| (1) \| **⃞** \| *No sabe* \| (99) \| | |
| **22** | | **A-** ¿Cuál es tu fruta favorita?  **B-** ¿Lavas tus frutas antes de comer - siempre, a veces, o nunca? | | Fruta: ………………………………….   \| **⃞** \| Nunca \| (0) \| **⃞** \| Siempre \| (2) \| \| --- \| --- \| --- \| --- \| --- \| --- \| \| **⃞** \| A veces \| (1) \| **⃞** \| *No sabe* \| (99) \| | |
| **26** | | ¿Caminas descalzo(a) – siempre, a veces, o nunca? | | \| **⃞** \| Nunca \| (0) \| **⃞** \| Siempre \| (2) \| \| --- \| --- \| --- \| --- \| --- \| --- \| \| **⃞** \| A veces \| (1) \| **⃞** \| *No sabe* \| (99) \| | |
| **27** | | ¿Cuándo estás en casa, usas zapatos o sandalias? | | \| **⃞** \| No usa \| (0) \| **⃞** \| Zapato \| (2) \| \| --- \| --- \| --- \| --- \| --- \| --- \| \| **⃞** \| Sandalias \| (1) \| **⃞** \| *No sabe* \| (99) \| | |
| **28** | | ¿En qué actividades del día estas descalzo(a)?   \| **⃞** *No aplica (NA)* \| \| --- \| | | A- Actividad: ………..………………………………….  B- Actividad: ………..………………………………….  C- Actividad: ………..…………………………………. | |
| **29** | | **A-** ¿Tus padres o tu profesor te dieron purgante (te desparasitaron)?  **B-** ¿En caso que si, cuándo fue la última vez que te dieron purgante? | | \| **⃞** \| Si \| (1) \| **⃞** \| No \| (0) \| **⃞** \| *No sabe* \| (99) \| \| --- \| --- \| --- \| --- \| --- \| --- \| --- \| --- \| --- \|  \|  \| Meses \| **⃞** \| Más de un año (13) \| **⃞**  **⃞** \| *No sabe (99)*  No aplica (NA) \| \| --- \| --- \| --- \| --- \| --- \| --- \| | |
| **30** | | **A-** ¿Cuántas personas viven en tu casa? Descríbelos…  **B-** ¿Cuántos niños menores de 12 años viven en tu casa? | | \|  \| Personas  (incluyéndote) \| **⃞** \| *No sabe (99)* \| \| --- \| --- \| --- \| --- \| \|  \| Niños \| **⃞** \| *No sabe (99)* \| | |
|  | **Comentarios:** | |  | |  |
|  |  | | | |  |
|  |  | | | |  |

**Annex 6:** Questionnaire (English Version)

